## Abstract

**Background:**

There are no available school-based alcohol and drug prevention programs with evidence of effectiveness among Aboriginal and Torres Strait Islander youth. To address this, we codeveloped the *Strong & Deadly Futures* well-being and alcohol and drug prevention program in partnership with an Indigenous creative design agency and 4 Australian schools.

**Objective:**

This paper presents the protocol to evaluate the effectiveness of *Strong & Deadly Futures* in reducing alcohol and other drug use and improving well-being among Aboriginal and Torres Strait Islander youth.

**Methods:**

The target sample will be 960 year 7 and 8 students from 24 secondary schools in Australia, of which approximately 40% (384/960) will identify as Aboriginal or Torres Strait Islander. The study design is a 2-group, parallel cluster randomized controlled trial with allocation concealment. Recruited schools will be block randomized (ratio 1:1), stratified by geographical remoteness, by an independent statistician. Schools will be randomized to receive *Strong & Deadly Futures*, a web-based alcohol and drug prevention and social and emotional well-being program that delivers curriculum-aligned content over 6 lessons via an illustrated story, or *health education as usual* (control). Control schools will be supported to implement *Strong & Deadly Futures* following trial completion. Surveys will be administered at baseline, 6 weeks, 12 months, and 24 months (primary end point) post baseline. Primary outcomes are alcohol use (adapted from the National Drug Strategy Household Survey), tobacco use (Standard High School Youth Risk Behavior Survey), and psychological distress (Kessler-5 Psychological Distress Scale). Secondary outcomes are alcohol and drug knowledge and intentions, alcohol-related harms, binge drinking, cannabis use, well-being, empowerment, appreciation of cultural diversity, and truancy.

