This paper presents a trial protocol (Australian New Zealand Clinical Trials Registry: ACTRN12620001038987) to evaluate the effectiveness of *Strong & Deadly Futures* in reducing AOD use and enhancing the emotional and social well-being of Aboriginal and Torres Strait Islander young people. This will be the first randomized controlled trial (RCT) of a school-based, culturally relevant alcohol and drug prevention program for Aboriginal and Torres Strait Islander adolescents. It is hypothesized that *Strong & Deadly Futures* will be more effective than an active control group (*health education as usual*) in delaying students’ uptake of alcohol and tobacco and reducing psychological distress over a 24-month period. The secondary aims are to examine the effects of *Strong & Deadly Futures* on students’ alcohol and drug knowledge and intentions, cannabis use, binge drinking and alcohol-related harms, well-being and empowerment, appreciation of cultural diversity, and truancy.

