#### Sample Size Calculations

The sample size has been calculated to account for cluster randomization using the methods developed by Heo and Leon [31] to detect group-by-time interactions in longitudinal cluster RCTs. To adequately power the trial for comparisons among Aboriginal and Torres Strait Islander students, a minimum of 264 Aboriginal or Torres Strait Islander students from 22 schools is required (ie, 12 Aboriginal or Torres Strait Islander students per school). This would achieve 80% power to detect a standardized between-group mean difference of 0.3 (*P*=.05) in primary alcohol (frequency of drinking a standard drink in the previous 6 months), tobacco (frequency of smoking a cigarette in the previous 6 months), and psychological distress (Kessler-5 Psychological Distress Scale) outcomes at the end of the trial with 4 measurement occasions. No effect size information was available for school-based prevention for Aboriginal and Torres Strait Islander students; thus, the estimated effect size of 0.3 was based on effects found for continuous alcohol outcomes in previous school-based prevention trials in mainstream populations [10,32]. Accounting conservatively for a higher student attrition rate than that observed in these trials of 30%, we will recruit 24 schools with an average of 16 Aboriginal or Torres Strait Islander students per school, and a total of 40 students per school. This totals 384 Aboriginal or Torres Strait Islander students, and a total sample of 960 students.

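### Three co-equal primary outcomes are each sized at P=.05 and 80% power with no allowance for multiplicity, so those figures hold only for separate outcome-by-outcome claims

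*Protocol article*

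**What the plan says.** The Methods paragraph of the abstract gives the outcomes on an equal footing: "Primary outcomes are alcohol use (adapted from the National Drug Strategy Household Survey), tobacco use (Standard High School Youth Risk Behavior Survey), and psychological distress". The Primary Outcomes section treats them the same way.

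The Sample Size Calculations section puts one error level and one power on all of them. It says "This would achieve 80% power to detect a standardized between-group mean difference of 0.3 (*P*=.05) in primary alcohol" and then continues the list with tobacco and psychological distress. The required sample is stated as follows: "a minimum of 264 Aboriginal or Torres Strait Islander students from 22 schools is required". The method is one designed "to detect group-by-time interactions in longitudinal cluster RCTs".

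The hypothesis under Objectives is that the program will do better than usual health education in delaying "uptake of alcohol and tobacco and reducing psychological distress over a 24-month period". The Analysis section assesses each outcome by its group-by-time interaction, with the primary analyses in Aboriginal and Torres Strait Islander students. The Assessments section makes 24 months the primary end point. Nothing in the article ranks the three outcomes, divides the 5% between them, or says how their results combine.

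**The concern.** The article asks about the effectiveness of the program as a whole, and the Discussion looks ahead to what follows if it proves effective. Three unadjusted tests at 5% give three chances of a false positive. If one significant result is enough for the overall statement, 5% is not the error rate of that statement. If all three are needed, 80% is not its power.

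The list of outcomes also shifts within the article. The Analysis section pairs alcohol and tobacco uptake with psychological well-being, and the Discussion hypothesizes effects on cannabis use and well-being, although cannabis use and well-being are secondary outcomes. With neither the family nor the combination rule fixed, there is room to choose the headline result after the data are seen.

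**Working it through.** **Inputs.** From Sample Size Calculations: level 0.05, power 80%, standardized difference 0.3, 22 schools of 12 students (264), 4 occasions, 30% attrition, 384 recruited. From the abstract: three primary outcomes. The article does not give sidedness (two-sided assumed), the within-student correlation, or the correlation between the three test statistics (assumed equal, range shown).

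**1. The plan's own figure.** A longitudinal cluster formula for a difference in slopes gives

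schools per arm = 2(1 - ρ)(z₀.₉₇₅ + z₀.₈₀)² / [m · Σ(t - t̄)² · (d/T)²].

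With m = 12, equally spaced occasions 0 to 3 (Σ(t - t̄)² = 5, T = 3) and d = 0.3, the denominator is 12 × 5 × 0.1² = 0.6, and (1.960 + 0.842)² = 7.849. At ρ = 0.58 this is 2 × 0.42 × 7.849 / 0.6 = 10.99, so 11 schools per arm, 22 schools and 264 students. The figure cannot be confirmed from the article alone because ρ is not given, but it is reachable at a plausible value. It uses the full 0.05 for a single outcome. Attrition is covered: 264 / 0.7 = 378, and 384 × 0.7 = 269. The steps below take the stated 80% at 0.05 as given, so each test statistic has mean 1.960 + 0.842 = 2.802 under the planned effect.

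**2. Any one outcome is enough, no adjustment.** Under independence the error is 1 - 0.95³ = 14.3%. The bound without any assumption is 3 × 0.05 = 15%.

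**3. All three are required, no adjustment.** Error stays at or below 5%. Under independence the power is 0.80³ = 51.2%. Without any assumption it lies between 3 × 0.80 - 2 = 40% and 80%.

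**4. Correlated test statistics** (simulation, 2 million draws, all effects 0.3 for power):

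| Correlation | Error, any of three | Power, all of three |
|---|---|---|
| 0 | 14.3% | 51% |
| 0.3 | 13.6% | 57% |
| 0.5 | 12.5% | 61% |
| 0.7 | 11.0% | 66% |
| 1 | 5% | 80% |

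Counting only false findings in favour of the program, the any-of-three error under independence is 7.3%. A single two-sided 5% test allows 2.5% in that direction.

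**5. Power under Holm at the planned size.** The first step uses 0.05/3 = 0.0167, critical value 2.394. Power for one outcome tested at that step is Φ(2.802 - 2.394) = 65.8%. Later steps use 0.025 and 0.05, so power per outcome is higher when the other outcomes also respond. By simulation with all three effects at 0.3:

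| Correlation | Per outcome | At least one |
|---|---|---|
| 0 | 75% | 96% |
| 0.5 | 73% | 87% |
| 0.7 | 73% | 82.5% |

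The 96% agrees with 1 - (1 - 0.658)³ = 0.960.

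**6. Restoring 80% for one outcome at 0.0167.** The factor is [(2.394 + 0.842)/2.802]² = 1.33, which is about 353 analysed students instead of 264, or about 504 recruited at 30% attrition.

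**The case against.** The strongest reply is that this is a condensed article. A multiplicity rule usually belongs in the analysis plan, which may exist and is not shown, so its absence here is no error. That stands. What remains is what the article itself fixes: level and power are set here, per outcome, at the full 0.05. An analysis plan that splits the 5% would no longer have the stated 80% for an outcome tested at the reduced level. One that requires all three would have less than 80% for its claim unless the tests were perfectly correlated.

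A second reply is that alcohol, tobacco and distress are distinct domains, each of which can carry its own claim. Read that way, 5% and 80% apply exactly as stated, and whether such claims need family-wise control is a matter of debate. This also stands, but the article does not say that it makes only separate claims.

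Four stronger readings are tempting and are not supported:

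- **That the stated figures fail however the plan is read.** Separate claims keep both. An all-three rule keeps the error at or below 5% and loses only power. An any-of-three rule loses only error control: unadjusted power for at least one outcome is 95-99% (correlation 0.5 to 0) if all effects are 0.3.
- **That 14% and 51% describe this trial.** They hold under independence and belong to alternative rules. Alcohol and tobacco use in the same students are probably positively correlated (an assumption), which makes 14% roughly a ceiling and 51% roughly a floor.
- **That the conjunction in the hypothesis is a decision rule requiring all three.** It is not stated as one.
- **That Holm cuts power to 66%.** That is the figure for an outcome tested at the smallest level only.

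**Conclusion.** The point holds in a limited form. The protocol sizes three co-equal primaries at an unadjusted 5% and 80% each, and these figures carry over to an overall statement of effectiveness under neither natural rule. With any one sufficing, the error is 11-14% for correlations from 0.7 to 0. With all three required, the error is held but power is 66% down to 51% over the same range. The conclusion rests on two-sided tests, equal correlations, normal test statistics and the protocol's own 80% at an effect of 0.3. It is worth correcting before outcomes are compared by arm, because a rule chosen afterwards carries little weight. It does not undermine the design or the data.

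**What to change.** State in the protocol and the analysis plan that the three primary outcomes are tested with the Holm procedure at a two-sided family-wise 5%, at 24 months, in the Aboriginal and Torres Strait Islander sample, and that conclusions are limited to the outcomes that pass. Name the family as alcohol use, tobacco use and psychological distress wherever the hypothesis is stated.

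Restate power under the plan's own assumptions: about 66% for an outcome tested at the first step (0.0167), about 73-75% per outcome if all three effects are 0.3, and about 82-96% for at least one (correlation 0.7 to 0). If the sponsor instead intends three separate claims with no overall verdict, the protocol should say so and make no general statement of effectiveness.

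The cost is a less favourable stated power per outcome. Enrolment and data collection do not change. Enlarging the trial to recover 80% at 0.0167 would take about 504 recruited students instead of 384, so restating the power is the practical course.

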**Results:**

The trial was funded by the National Health and Medical Research Council in January 2019, approved by the Human Research Ethics Committee of the University of Sydney (2020/039, April 2020), the Aboriginal Health and Medical Research Council of New South Wales (1620/19, February 2020), the Western Australian Aboriginal Health Ethics Committee (998, October 2021), and the ethics committees of each participating school, including the New South Wales Department of Education (2020170, June 2020), Catholic Education Western Australia (RP2020/39, November 2020), and the Queensland Department of Education (550/27/2390, August 2021). Projected dates of data collection are 2022-2024, and we expect to publish the results in 2025. A total of 24 schools have been recruited as of submission of the manuscript.

**Conclusions:**

This will be the first cluster randomized controlled trial of a culturally inclusive, school-based alcohol and drug prevention program for Aboriginal and Torres Strait Islander youth; therefore, it has significant potential to address alcohol and other drug harms among Aboriginal and Torres Strait Islander youth.

**Trial Registration:**

Australian New Zealand Clinical Trials Registry ACTRN12620001038987; https://www.anzctr.org.au/Trial/Registration/TrialReview.aspx?id=380038&isReview=true

**International Registered Report Identifier (IRRID):**

PRR1-10.2196/34530

## Introduction

### Background

Despite the ongoing impacts of colonization, disempowerment, and inequity, strong cultural and community connections have persisted as sources of resilience for Aboriginal and Torres Strait Islander young people [1,2]. Nonetheless, intergenerational trauma has contributed to poorer emotional and social well-being, with alcohol and other drug (AOD) use identified as both a risk factor for and a consequence of mental illness among Aboriginal and Torres Strait Islander youth [3]. Over the past decade, encouraging trends have been observed with declines in binge drinking (≥5 standard drinks, each containing 10 g of ethanol) and tobacco use reported among young Aboriginal and Torres Strait Islander adolescents [4]. However, Aboriginal and Torres Strait Islander youth continue to experience disproportionate harm from AOD use and, combined with an average earlier age of use [5,6], are at increased risk of substance use disorders later in life [7-9]. To reduce this inequity, it is critical that alcohol and drug prevention initiatives are designed to be culturally relevant for Aboriginal and Torres Strait Islander adolescents to empower them to reach their full potential.

Schools are an ideal setting to deliver alcohol and drug prevention education [10,11]. School-based programs have demonstrated efficacy in preventing or delaying the uptake of AODs and improving attitudes and knowledge of related harms [12-14]. However, a recent international systematic review identified no well-being and drug prevention programs available for Aboriginal and Torres Strait Islander students that are culturally appropriate and effective [15].

### Objectives

To address this gap, *Strong & Deadly Futures* was codeveloped in partnership with an Indigenous Australian creative design agency (Gilimbaa) and with the leadership of Aboriginal and Torres Strait Islander youth (41/77, 53% Indigenous [16]) and staff at 4 Australian secondary schools. The development was informed by stakeholder consultations (17/42, 40% Aboriginal or Torres Strait Islander) and overseen by an advisory group of experts in Aboriginal health, drug prevention, and research (6/16, 38% Aboriginal or Torres Strait Islander). The resulting program, *Strong & Deadly Futures,* is a culturally inclusive curriculum program that aims to reduce harm from AOD use by enhancing coping skills and preventing substance use initiation over the vulnerable adolescent period. The program features web-based delivery to enhance engagement, reach, and implementation fidelity and incorporates core skill development and harm minimization components from the effective *Climate Schools* drug prevention programs [17-25]. It also includes strategies to promote social and emotional well-being, such as coping with stress and effective decision-making. Drawing on feedback from our Aboriginal and Torres Strait Islander stakeholders, *Strong & Deadly Futures* incorporates cultural components to foster pride and appreciation of Aboriginal and Torres Strait Islander culture. Although Aboriginal and Torres Strait Islander culture is central to the program, it was designed to be culturally inclusive so it can be delivered in classrooms with both Aboriginal and non-Indigenous students, reflecting the most common classroom setting experiences of Aboriginal students in Australia. A pilot study showed that *Strong & Deadly Futures* was acceptable and feasible to implement in culturally diverse classrooms, with postprogram improvements observed in students’ knowledge of alcohol and drug harms and overall well-being (unpublished data).

This paper presents a trial protocol (Australian New Zealand Clinical Trials Registry: ACTRN12620001038987) to evaluate the effectiveness of *Strong & Deadly Futures* in reducing AOD use and enhancing the emotional and social well-being of Aboriginal and Torres Strait Islander young people. This will be the first randomized controlled trial (RCT) of a school-based, culturally relevant alcohol and drug prevention program for Aboriginal and Torres Strait Islander adolescents. It is hypothesized that *Strong & Deadly Futures* will be more effective than an active control group (*health education as usual*) in delaying students’ uptake of alcohol and tobacco and reducing psychological distress over a 24-month period. The secondary aims are to examine the effects of *Strong & Deadly Futures* on students’ alcohol and drug knowledge and intentions, cannabis use, binge drinking and alcohol-related harms, well-being and empowerment, appreciation of cultural diversity, and truancy.

## Methods

### Overview

*Strong & Deadly Futures* will continue to be closely developed with Aboriginal and Torres Strait Islander communities. The first phase of the project involves establishing partnerships with local Aboriginal and Torres Strait Islander organizations to conduct community consultations and seek feedback on the program. This feedback will inform adaptations to the program to align it with local priorities and contexts. The second phase involves trialing the adapted program in a school-based RCT. An Aboriginal Reference Group will provide oversight throughout both stages of the project.

### Aboriginal and Torres Strait Islander Leadership

#### Aboriginal Reference Group

An Aboriginal Reference Group will provide oversight and guidance through the consultation, school-based trial, and dissemination phases of the study. The Reference Group will comprise experts involved in the development of the *Strong & Deadly Futures* program and representatives from the local Aboriginal Community Controlled Health Services (ACCHS) or Aboriginal and Torres Strait Islander stakeholder organizations in participating communities. The Aboriginal Reference Group will meet annually throughout the study duration, with the possibility of out-of-session meetings as required.

#### ACCHS Partnerships

In line with best practices in Aboriginal and Torres Strait Islander health research [26], we will ask the local ACCHS or other relevant Aboriginal or Torres Strait Islander stakeholder organizations to consent to the trial proceeding in their community. The ACCHS will be invited to partner with the research team to conduct consultations in their community, and staff will be invited to participate in consultation sessions. A representative from each ACCHS will be invited to sit in on the Aboriginal Reference Group.

#### Local Aboriginal or Torres Strait Islander Facilitators

An Aboriginal or Torres Strait Islander facilitator will be employed in each community to conduct local consultations and support research implementation in schools. Facilitators may be recruited from the local ACCHS or the participating trial school. The consultation role will involve recruiting local community members and organizing and facilitating the consultations. School-based project support will include supporting teachers with the cultural aspects of the program, as well as assisting with survey administration and measurement of implementation fidelity through lesson observations. Facilitators will attend a series of training workshops with the research team before community consultations and commencement of the trial and will be provided with a handbook outlining the research process, methods, and program content. Facilitators will receive regular supervision and mentoring from the research team and will be provided with opportunities to participate in conferences and workshops throughout the study.

### Phase 1: Community Consultations

Consultations will be conducted in each community to obtain local feedback to inform adaptations to the program to align with the local context.

#### Participants and Recruitment

Within the local community of schools enrolled in the trial, facilitators will conduct 2 separate consultation sessions with (1) Aboriginal or Torres Strait Islander adults and (2) Aboriginal or Torres Strait Islander young people aged 12-16 years. Participants will be recruited using a variety of channels, including through the local ACCHS, word of mouth, social networking, and by distributing flyers at community events and health or youth services. Written consent from adults, young people, and parents or carers of young people will be obtained before the consultations.

The research team will also conduct 1:1 semistructured interviews with 1-2 teaching staff from the participating trial school to discuss the feasibility and acceptability of the program in the classroom. Written consent will be obtained before the interviews.

#### Procedure

Consultations with Aboriginal and Torres Strait Islander community members will be conducted using a culturally appropriate research yarning method [27,28]. Research yarning will involve obtaining stories and experiences related to the social and emotional well-being of young people in the community and feedback to inform tailoring of the program to the local context. The yarning circles will be conducted by the local facilitator and audio-recorded if the participants consent. Where possible, a member of the research team will also attend to take notes. If preferred by the community, consultations will be conducted with participants and facilitators of the same gender. Furthermore, 1 or 2 teaching staff from each school will also participate in 1:1 semistructured interviews, conducted on the web by the research team, audio-recorded (with permission), and transcribed.

